## Study AIMS

The aim of this study is to examine the impact of AE training on suicide risk and related predictors in individuals with SZ.

*Hypothesis 1.1*: At 12 weeks, subjects in the AE training will significantly reduce their suicide risk compared to controls.

*Hypothesis 1.2*: Increases in aerobic fitness will predict reduction in suicide risk.

*Hypothesis 2.1*: At 12 weeks, subjects in the AE training will significantly improve their depressed mood, sleep quality and quantity, and executive functioning compared to controls.

*Hypothesis 2.2*: AE-induced improvements in suicide risk from baseline to 6 weeks to 12 weeks will be mediated by decreases in depressed mood and improvement in sleep quality and quantity, and executive functioning.

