## Randomization

After signing informed consent and undergoing baseline assessment of primary and secondary outcome measures, eligible participants will be assigned 1:1 randomly via computer to one of two 12-week, 3×/week, 1-h interventions: (1) aerobic exercise intervention (AE) or (2) a stretching and toning control intervention (ST). Participants will receive intervention assignment via a secure telephone call.

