### Sample size calculations

A power analysis was considered for determining sample size. However, a power analysis was ultimately determined not to be appropriate for the current trial due to the lack of direct data on the relationship between aerobic exercise and reduction in suicide risk. Additionally, recruitment and sample size for this protocol is associated with the ongoing parent R01-funded protocol.

The sample size for the parent R01-funded study is 200 outpatient individuals with SZ. This sample size was determined based on a focus on cognition as the primary outcome, specifically the MCCB total composite score. Prior literature suggests average scores of individuals with SZ fall between 1 and 2.5 standard deviations lower than MCCB averages. Therefore, a 0.50 standard deviation was chosen as a meaningful target effect size for powering the trial. The pilot for the parent study found a large effect size for the AE intervention group compared to controls suggesting a 0.893 standard deviation improvement in the intervention group compared to controls. The parent study sample size calculations assumed a loss-to-follow-up rate of 20% with 80 participants remaining in each arm (100 × 0.8). According to these calculations, the parent study is powered to detect moderate or larger effect size difference with > 80% power. The current study retains confidence that the sample size will provide adequate power to detect a clinically meaningful effect size for suicide risk as the primary outcome.

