### Data analyses

All primary analyses will be carried out on an intent-to-treat (ITT) basis, i.e., all subjects randomized will be analyzed according to the treatment they were assigned regardless of adherence to treatment. Level of fidelity to training intensity, accounting for adherence, will be controlled for in these analyses. All statistical tests will be two-sided with critical value α = 5%.

Mixed effects regression will be used to model suicide risk as a function of time (0, 6, 12 weeks), treatment group (AE or ST), interaction of time by treatment group, and site (1, 2, 3, or 4). The efficacy of AE to improve suicide risk in people with SZ will be represented by the statistical significance of the time by treatment group interaction. The effect of AE on mood, sleep, and executive functions will be tested by conducting similar analyses, i.e., mixed effects regression across 0, 6, and 12 weeks.

Mediators in the relationship between AE and suicide risk will be identified by multi-step process. A mediation effect will be estimated by taking the expected value of the total effect of AE on changes in suicide risk and subtracting the effect when changes in mood, sleep, and executive functioning have been controlled. These mediation effects will be tested by fitting a Structural Equation Model (SEM) with change in depressed mood, sleep, and executive function from baseline to 6 weeks as mediators of the relationship between AE treatment and change in suicide risk from baseline to 6 weeks as well as later changes in suicide risk from 6 to 12 weeks using MPlus version 8. The mediator-outcome relationship can be confounded by other time-varying covariates (e.g., BMI changes), and these will also be adjusted for in the model.

Change in suicide risk from baseline will be modeled using mixed effect regression predicted by contemporaneous change in aerobic fitness from baseline as measured by VO_2_max tests (at 6 and 12 weeks), controlling for treatment group and other covariates. The ability of aerobic fitness improvement to predict reduction in suicide risk will be represented by a statistically significant positive regression coefficient for change in aerobic fitness.

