Demographic and other biologically relevant baseline variables (e.g., sex, depression, and smoking status) will be included as control variables if there is evidence of randomization imbalance in them. Multiple imputation will be used to handle missing data using the MI and MIANALYZE SAS procedures.

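### Efficacy is judged on the time-by-group interaction with time coding unstated, not on the week-12 difference of Hypothesis 1.1, and the baseline suicide-risk score goes unused for precision

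*Protocol article*

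**What the plan says.** Study AIMS, Hypothesis 1.1, places the claim at one time point: "At 12 weeks, subjects in the AE training will significantly reduce their suicide risk compared to controls".

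The Data analyses section of the protocol article will use mixed effects regression to "model suicide risk as a function of time (0, 6, 12 weeks), treatment group (AE or ST), interaction of time by treatment group", plus site. Efficacy "will be represented by the statistical significance of the time by treatment group interaction". No week-12 contrast is named, and the section does not say whether time enters as a factor or as a continuous variable.

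Week 0 is one of the modelled outcome times and group has its own main effect, so the arms' baseline means are left free to differ. The same section says that demographic and other baseline variables "will be included as control variables if there is evidence of randomization imbalance in them"; its examples are sex, depression and smoking status. The baseline suicide-risk score is not named as a covariate, and no common baseline mean is stated.

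**The concern.** The rule that decides the trial should answer the question that the trial asks. Hypothesis 1.1 asks about week 12. An interaction over three visits asks whether the arms' courses differ anywhere across those visits, or, if time is linear, whether their slopes differ. Neither is stated to be the week-12 difference, and the two codings can lead to different conclusions from the same data.

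The second part is about precision. Randomization follows the baseline assessment, so the arms have the same expected baseline. A model that estimates a separate baseline mean for each arm does not use that fact, and its week-12 effect behaves like a comparison of change scores. The Sample size calculations section declines a power analysis for suicide risk and takes the sample size from the parent study, so efficient use of the data already planned is one of the few ways left to gain power.

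**Working it through.** **Inputs from the protocol article**
- Allocation: "eligible participants will be assigned 1:1 randomly via computer" (Randomization).
- Two-sided testing at the 5% level (Data analyses).
- 160 participants (Methods/design), so 80 per arm.
- From the parent study's cognition outcome (Sample size calculations): "a 0.50 standard deviation was chosen as a meaningful target effect size for powering the trial", and the calculation "assumed a loss-to-follow-up rate of 20% with 80 participants remaining in each arm (100 × 0.8").

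**Assumptions not in the documents**
- The parent study's 0.5 SD is applied to suicide risk.
- Its 20% loss is applied to this trial: 80 × 0.8 = 64 per arm. Results for 80 per arm are also shown.
- Correlation ρ between any two visits is 0.3 to 0.7 (compound symmetry), SD is 1 at every visit, scores are approximately normal, and data are complete for the n analysed.

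**Reproducing the stated figure.** For 80 per arm and 0.5 SD, the noncentrality is n·d²/2 = 80 × 0.25 / 2 = 10. Power is Φ(√10 − 1.96) = Φ(1.20) = 88.5%, which agrees with the parent study's claim of more than 80%.

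**Noncentrality of each test.** Let d6 and d12 be the true differences at weeks 6 and 12, in SD units.
- (a) 2-df interaction, free baseline: n(d6² − d6·d12 + d12²) / [3(1 − ρ)]
- (b) 1-df week-12-minus-baseline contrast, free baseline: n·d12² / [4(1 − ρ)]
- (c) 1-df week-12 contrast, baseline adjusted or constrained equal: n·d12² / [2(1 − ρ²)]

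**Effect at week 6 only (d6 = 0.5, d12 = 0), categorical time.** At n = 64 and ρ = 0.5, (a) is 64 × 0.25 / 1.5 = 10.67, which gives 84% rejection. Tests (b) and (c) have noncentrality 0 and reject in 5%.

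| Rejection by the 2-df test | ρ = 0.3 | ρ = 0.5 | ρ = 0.7 |
|---|---|---|---|
| 64 per arm | 70% | 84% | 97% |
| 80 per arm | 79.5% | 91.5% | 99.2% |

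**Effect growing evenly (d6 = 0.25, d12 = 0.5), 64 per arm, ρ = 0.5**
- (a) 64 × 0.1875 / 1.5 = 8.0 on 2 df: 72%
- (b) 64 × 0.25 / 2 = 8.0 on 1 df: 81%
- (c) 64 × 0.25 / 1.5 = 10.67 on 1 df: 90%

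**Effect full by week 6 and held (0.5 at both), same settings**
- (a) 64 × 0.25 / 1.5 = 10.67 on 2 df: 84%
- (b) 81% and (c) 90%, as above

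**Linear time.** The visits are equally spaced. Under compound symmetry and complete data the slope contrast weights the visits (−1, 0, +1), so it is test (b). Its power is 81% for the evenly growing effect, and it rejects in 5% when the effect is at week 6 only.

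**Variance of the week-12 effect, in units of 2·SD²/n.** With a free baseline it is 2(1 − ρ). With baseline adjusted or constrained it is 1 − ρ². The ratio is (1 + ρ)/2.

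| ρ | Free | Adjusted | Ratio | Reduction |
|---|---|---|---|---|
| 0.3 | 1.40 | 0.91 | 0.65 | 35% |
| 0.5 | 1.00 | 0.75 | 0.75 | 25% |
| 0.7 | 0.60 | 0.51 | 0.85 | 15% |

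For d12 = 0.5 and 64 per arm, power moves from (b) to (c) as follows: 67% to 84% at ρ = 0.3, 81% to 90% at ρ = 0.5, and 95.5% to 97.7% at ρ = 0.7.

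**The case against.** **The coding of time is open, and this limits the first part.** A reader might infer that the rule, as written, lets the trial claim efficacy with nothing at week 12. The text supports that only if time is categorical. The levels of time are listed in the same way as those of group and site, which points to a factor but does not settle it. Under linear time the week-6-only problem disappears in the model used here, and what remains is reliance on a straight-line course.

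**The week-6-only pattern is extreme.** The Interventions section keeps the highest training target from week 4 through week 12, so nothing is withdrawn between the two later visits, and the documents give no reason to expect full reversal. This stands. The example shows what the rule permits, not what is likely.

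**A reader might infer that the interaction always has less power.** It does not. If the effect is full by week 6 and held, the 2-df test slightly beats the unadjusted week-12 contrast (84% against 81%), though it stays below the baseline-adjusted one (90%).

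**A reader might infer that the free baseline biases the result.** It does not under randomization. Keeping baseline in the outcome vector is a standard and valid choice, and some such details are commonly left to an analysis plan. But the article does set out the model terms and the decision rule, and a more precise analysis of the same data is available.

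**A reader might also infer that a significant result in the wrong direction would count as efficacy.** The rule names no sign, but the sentence speaks of improving suicide risk and Hypothesis 1.1 of reducing it. A two-sided test read with the sign of its estimate is ordinary practice.

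**The inputs are borrowed.** The effect size and loss rate come from a cognition outcome, and ρ is assumed. Eligibility sets no minimum suicide risk, so scores may cluster near zero and the normal-theory percentages may not carry over exactly. This also stands.

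**Conclusion.** The concern holds in two parts of different strength.

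- **Test against hypothesis.** The declared criterion is not the week-12 difference of Hypothesis 1.1, and the coding of time that would decide how far apart they are is not given. If time is categorical, the gap is material: 70% to 97% rejection for a week-6-only effect at 64 per arm, against 5% for a week-12 contrast. If time is linear, the gap is mainly the straight-line assumption.
- **Precision.** This part holds under either coding. Using the baseline score would cut the variance of the week-12 effect by 35%, 25% or 15% at ρ of 0.3, 0.5 or 0.7. The gain is small in power terms where ρ is high.

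The mismatch follows from the text alone. The sizes rest on the assumptions listed with the calculation and illustrate scale; they are not this trial's power, for which the documents give no figure.

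**What to change.** Name the model-based AE minus ST difference in suicide risk at week 12 as the single primary test. State that time is categorical. Either enter the baseline C-SSRS score as a covariate, with weeks 6 and 12 as outcomes, or keep week 0 in the outcome vector with a common baseline mean across arms. Make this part of the primary model regardless of observed imbalance. Report the week-6 difference and the overall time-by-group interaction as supportive.

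This is a change of analysis wording, and it needs no new data because the C-SSRS is already collected at baseline. The one small cost is that the primary test gives up sensitivity to a benefit seen only at week 6; the supportive analyses would still show it.

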### Suicide risk

Blinded Clinical Raters will administer suicide risk measures to all participants during baseline, 6-week, and 12-week research visits. As part of the protocol, the clinical raters will obtain certification in the administration of the suicide, clinical, and other measures prior to initiating the study, as well as annually. For assessments of suicide risk, all current and future raters will complete the certificate training for the C-SSRS. Additionally, [name], an expert on suicide risk, will be available for inquiries/supervision regarding assessment of suicide risk throughout the study duration.

The Columbia Suicide Severity Rating Scale (C-SSRS) will serve as a primary outcome measure of suicide risk [56]. The C-SSRS is a 12-item, semi-structured interview that measures 4 suicide risk-related domains: ideation severity, ideation intensity, behavior, and lethality. To address potential safety concerns associated with recruitment of individuals with higher suicide risk, all participants will also be administered the C-SSRS by phone at 3 and 9 weeks after baseline. Additional secondary measures of suicide risk will include the InterSePT Scale for Suicidal Thinking (ISST), the Beck Suicide Ideation Scale (BSIS), Beck Hopelessness Scale (BHS), and the Reasons for Living Inventory (RLF) [57–60]. All the suicide risk measures will be administered at baseline, and after 6 and 12 weeks in parallel to the assessments of the parent R01-funded protocol.

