### Psychiatric symptoms

Symptom severity will be assessed with the Positive and Negative Syndrome Scale (PANSS) along with the Beck Depression Inventory (BDI) and Beck Anxiety Inventory (BAI). These assessments will be administered by blinded clinical raters at baseline, 6 weeks, and 12 weeks.

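### The 6-12 week mediation path shares the week-6 visit with its mediator at opposite sign; unless earlier suicide risk is conditioned on, it can be biased toward the reversed direction

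*Protocol article*

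**What the plan says.** Study AIMS, Hypothesis 2.2, holds that improvements in suicide risk under aerobic exercise (AE) over weeks 0, 6 and 12 "will be mediated by decreases in depressed mood and improvement in sleep quality and quantity, and executive functioning". Data analyses gives the model. It is an SEM with "change in depressed mood, sleep, and executive function from baseline to 6 weeks as mediators", and the outcomes are "change in suicide risk from baseline to 6 weeks as well as later changes in suicide risk from 6 to 12 weeks". On adjustment it says: "The mediator-outcome relationship can be confounded by other time-varying covariates (e.g., BMI changes), and these will also be adjusted for in the model". It does not say whether suicide risk at week 0 or 6, or the 0-6 week change in risk, predicts the 6-12 week change.

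Mediators and outcome are measured on one schedule. Under Suicide risk: "All the suicide risk measures will be administered at baseline, and after 6 and 12 weeks in parallel to the assessments" of the parent study. Under Psychiatric symptoms, which covers the depression inventory: "These assessments will be administered by blinded clinical raters at baseline, 6 weeks, and 12 weeks". Sleep data and the cognitive battery follow the same three visits. All tests are two-sided at 5%.

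**The concern.** Write M for a mediator and Y for suicide risk, both scored so that higher is worse. The later path has M6 - M0 predicting Y12 - Y6, so week 6 is added in the predictor and subtracted in the outcome. Suppose a participant is temporarily better at week 6 in both mood and suicide risk. That participant shows a mediator improvement, followed by a rise in suicide risk as the temporary state passes. The result is a negative association between the two changes without any effect of mood on later risk.

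The 6-12 week path is the only part of the model in which the mediator change precedes the outcome change, so a claim of mediation in the right time order depends on it. If it is biased, it could suggest that better mood leads to higher later suicide risk, or it could cancel a real protective effect.

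**Working it through.** **Inputs from the article.** 160 participants, 1:1 allocation, visits at weeks 0, 6 and 12, two-sided 5%. The parent study assumes 20% loss; applied here, 160 x 0.8 = 128, or 64 per arm.

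**Assumptions, not in the article.**
- One mediator and normal scores, with half trait and half visit-level (state) variance.
- Equal state variance for M and Y.
- Same-visit state correlation rho from 0 to 0.5.
- A common six-week autocorrelation phi.
- AE moves the mediator by 0.5 SD. This figure is borrowed from the parent study's cognitive target.

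**The plan's own figure.** The mediation model has no stated error rate or power. The only design figure is the parent study's power above 80% for 0.50 SD with 80 per arm. A two-sample calculation gives 88.5%, which agrees (64 per arm gives 80.7%).

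**Bias of the unconditioned path.** With state variance s²:
- Cov(M6 - M0, Y12 - Y6) = s²·rho·(phi - 1 - phi² + phi) = -s²·rho·(1 - phi)²
- Var(M6 - M0) = 2s²(1 - phi)
- Slope = -rho(1 - phi)/2

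The trait part cancels. At phi = 0 the slope is -0.15 for rho 0.3 and -0.25 for rho 0.5. At phi = 0.3 it is -0.105 and -0.175.

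**Rejection of a null path.** The two change scores have equal variance, so the standard error is about √((1 - slope²)/n). For n = 128, phi = 0 and rho = 0.3 this is √(0.9775/128) = 0.087. Then 0.15/0.087 = 1.72 and P(Z > 1.96 - 1.72) is about 40%. Simulation agrees:

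| rho (phi = 0) | null slope | path rejects, n = 128 | path rejects, n = 160 | indirect effect rejects, n = 160 |
|---|---|---|---|---|
| 0 | 0 | about 5% | 5% | 5% |
| 0.1 | -0.05 | 7-9% | 10% | 9% |
| 0.2 | -0.10 | 21% | 25% | 22% |
| 0.3 | -0.15 | 37-40% | 47% | 41% |
| 0.5 | -0.25 | 82% | 90% | 79% |

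For rho of 0.2 and above, nearly all rejections are in the reversed direction. With phi = 0.3 and n = 128, the path rejects 21% at rho 0.3 and 51% at rho 0.5.

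The indirect effect was tested by joint significance of the AE-to-mediator path and the lagged path. Its inflation needs AE to move the mediator. If AE does not, at n = 160 and rho 0.3 to 0.5 the indirect test rejects only 2-4%, although the lagged path alone still rejects 48-89%.

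**Masking.** The bias adds to the true slope. A true 0.15 with rho 0.3 is estimated as 0.15 - 0.15 = 0, and a true 0.25 with rho 0.5 as 0.25 - 0.25 = 0. At n = 128, a true slope of 0.25 and rho 0.3, power for the lagged path is about 20% unconditioned and 85-89% with earlier risk in the equation.

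**After conditioning on Y6 - Y0.** The two further covariances are Cov(M6 - M0, Y6 - Y0) = 2s²·rho·(1 - phi) and Cov(Y6 - Y0, Y12 - Y6) = -s²(1 - phi)², with Var(Y6 - Y0) = 2s²(1 - phi). The numerator of the partial slope, divided by s², is -rho(1 - phi)² + rho(1 - phi)² = 0. Simulated null rejection is 4.2-5.8% in every cell with a common phi. Conditioning on week 6 alone is not enough: reversed-direction rejection stays at 16% to 59%.

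**The case against.** **The faulty equation is not written out.** The article gives windows, mediators, an open-ended list of covariates and the software, but no path list. A path from the first risk change to the second is neither included nor excluded, and a condensed article may leave such paths to the full plan. This stands, and it makes the point conditional. It does not remove the point, because the windows are fixed in the text and the one example of adjustment is of a different kind. A mere residual covariance between the two risk changes would not remove the bias.

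**The correlation is unknown.** Mediator and outcome are different variables, so a shared visit does harm only if their within-person deviations are correlated. The Background lists low mood, poor sleep and poor cognition as suicide predictors, which makes this plausible, most clearly for mood. No value is given, and at rho = 0 the test holds its level.

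**The figures may be too high.** Entry does not require raised suicide risk, so many scores on the primary suicide scale (C-SSRS) may be zero. With an assumed 70-80% at zero and n = 128, rejection falls to 21-16% at rho 0.3 and 49-38% at rho 0.5. Each C-SSRS rating also covers the time since the last one, with phone ratings at weeks 3 and 9. The week-6 score is therefore less of a snapshot. Both limits stand; the bias becomes smaller but does not vanish.

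**The remedy is imperfect.** If mediator and outcome states persist differently, some bias remains. With autocorrelation 0.6 for the mediator, 0.2 for the outcome and rho 0.5, null rejection falls from about 89% to roughly 9-18%, not to 5%. With the two values swapped, conditioning changes little (10% to 7%). Week-6 risk is also a post-treatment variable, so the meaning of the lagged coefficient changes. Both stand as costs.

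**Conclusion.** The point holds conditionally. The article fixes windows that share week 6 at opposite sign. If the 6-12 week equation omits earlier suicide risk, and if mediator and risk fluctuate together at a visit, the lagged path is biased toward the reversed sign by about -rho(1 - phi)/2. At n = 128 and phi = 0, null rejection runs from about 5% at rho 0 to 82% at rho 0.5. These figures rest on the assumed rho, phi, variance split, normal scores and single mediator. They are a range, not the trial's error rate.

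A reader might infer more in three ways, and the documents support none of them:
- That the article commits to the unconditioned model. It is silent on the paths.
- That the mediation test over-rejects whenever there is no mediation. The path needs rho above zero, and the indirect test is inflated only if AE also moves the mediator.
- That the efficacy result is in doubt. The time-by-treatment comparison and the 0-6 week part of the SEM do not use this path. Only the 6-12 week part of Hypothesis 2.2 is affected.

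This is a worthwhile correction to a mechanistic analysis, not a fault in the main comparison.

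**What to change.** State the later equation explicitly. Either model week-12 suicide risk on treatment, 0-6 week mediator change, and suicide risk at weeks 0 and 6, or keep the change scores and add a path from the 0-6 week to the 6-12 week risk change. If the full plan already contains such a path, saying so is enough.

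The cost is one sentence and one or two parameters, with no new data. The lagged coefficient becomes an effect given earlier risk, so any mediated effect carried through the 0-6 week risk change must be read from that separate path. The text should also acknowledge that some bias can remain if mediator and outcome persist differently over six weeks.

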### Suicide risk safety

To address potential safety concerns associated with recruitment of individuals with higher suicide risk, all participants will also be administered a suicide risk assessment (i.e., C-SSRS) by phone at 3 and 9 weeks after baseline, in addition to the suicide risk assessments scheduled during research visits at baseline, 6 weeks, and 12 weeks. All assessments will capture suicidal symptoms from the last administration of the instrument. The raters will consult with the site PI regarding the detection of any suicidality, including passive suicidality. Any subject with a C-SSRS score equal or greater than “4” (Active Suicidal Ideation with Some Intent to Act, without Specific Plan) will require a consultation with [name], the project’s Medical Director, and [name], the project’s suicide expert. Any subject that scores a “5” (Active Suicidal Ideation with Specific Plan and Intent) and judged to be actively suicidal will require urgent clinical evaluation for the possibility of hospitalization, and he/she will be escorted to the closest ER by study staff. [name] has extensive clinical experience treating veterans at high risk for suicide and is available by cell phone 24/7, should clinical consultation regarding study participants be necessary.

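### The success criterion for Hypothesis 1.2 asks for a positive coefficient, but with change read as follow-up minus baseline the hypothesis needs a negative one

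*Protocol article*

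**What the plan says.** Hypothesis 1.2 (Study AIMS) reads: "Increases in aerobic fitness will predict reduction in suicide risk".

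The model for it is in the last paragraph of that name under Data analyses. For the outcome: "Change in suicide risk from baseline will be modeled using mixed effect regression". The predictor follows in the same sentence: "predicted by contemporaneous change in aerobic fitness from baseline as measured by VO_2_max tests (at 6 and 12 weeks". The model also controls for treatment group and other covariates. The next sentence gives the decision rule. Fitness improvement is taken to predict a reduction in suicide risk if there is a "statistically significant positive regression coefficient for change in aerobic fitness".

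On the outcome scale, the Suicide risk section says: "The Columbia Suicide Severity Rating Scale (C-SSRS) will serve as a primary outcome measure of suicide risk". Suicide risk safety gives two of its levels. Level 4 is ideation with some intent but no specific plan and triggers a consultation. Level 5 is "Active Suicidal Ideation with Specific Plan and Intent" and, if the participant is judged actively suicidal, triggers urgent evaluation.

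**The concern.** The outcome is described as a change from baseline in the same terms as the predictor. The ordinary meaning of both is follow-up minus baseline. On that meaning a reduction in risk is a negative number, and a hypothesis that links higher fitness to lower risk predicts a negative slope. The article asks for a positive one.

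The article ties the claim to the sign of the coefficient, so the sign decides how the result is read. A literal application would treat an adverse association as support for the hypothesis and a favourable one as lack of support. In a trial whose subject is suicide risk, a published rule should not leave that to be sorted out once the results are known.

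**Working it through.** No figure in the plan has to be reproduced. The check is one of sign.

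**Inputs**

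- Direction of the hypothesis: fitness up, risk down (Study AIMS, Hypothesis 1.2).
- Outcome and predictor: both are changes from baseline, with no subtraction order given for either (Data analyses).
- Direction of VO2max: higher is better. The Background calls a pilot gain of 3.82 mL/kg/min an 18% improvement.
- Direction of the C-SSRS: higher is worse, from the order of levels 4 and 5 in Suicide risk safety.
- Tests: two-sided at 5% (Data analyses).

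**Algebra**

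Write Δrisk = b × ΔVO2max + terms for arm and covariates, with Δ = follow-up minus baseline. Hypothesis 1.2 says that a larger ΔVO2max goes with a lower Δrisk. Hence b < 0. The article requires b > 0.

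**Illustration with two participants in the same arm** (the C-SSRS values are invented)

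- A: ΔVO2max = 0, C-SSRS 5 → 5, so Δrisk = 0.
- B: ΔVO2max = 3.82, C-SSRS 5 → 4, so Δrisk = −1.
- Slope = (−1 − 0) / (3.82 − 0) = −0.26. The hypothesis is met and the stated rule is not.

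Now let A stay at 4 and B go from 4 to 5 with the same fitness gain. The slope is (+1 − 0) / (3.82 − 0) = +0.26. The stated rule is met and the hypothesis is contradicted.

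**Same data, outcome recoded as reduction** (baseline minus follow-up)

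In the first example B's outcome becomes +1 and the slope +0.26. *Positive* is then the right word.

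**Mixed model**

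Data were simulated for 160 participants at 6 and 12 weeks, with a random intercept and adjustment for arm and time. The assumed true slope was −0.15 points per mL/kg/min. That value is not in the article, and only its sign matters.

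| Outcome coding | Estimated b |
|---|---|
| Follow-up minus baseline | −0.154 |
| Baseline minus follow-up | +0.154 |

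The p-value is identical in the two rows. The simulation is not evidence about the trial, because it returns the sign that was put in. It confirms only that recoding flips the sign and changes nothing else.

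**The case against.** The strongest reply is that the authors meant a reduction score. The sentence with the criterion itself pairs improvement in fitness with reduction in risk. If both variables are scored so that positive means better, *positive* is correct. Such scoring is coherent when one scale is higher-worse and the other higher-better. This stands as a possible intention, and it makes a reduction score an equally valid repair. It does not remove the mismatch. The sentence that defines the outcome speaks of change from baseline, uses the same phrase for fitness, and no other section states a reversed coding.

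A second reply is that subtraction order is a detail for the analysis plan. That is fair for the order alone. Here, however, the article itself fixes the sign of the success criterion, so the point is about something stated, not something left out.

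A third is that higher-is-worse is documented only in part. This also stands. Levels 4 and 5 describe ideation severity, while the Suicide risk section lists four C-SSRS domains and does not say which score enters this model.

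A reader might go further and infer that the trial would report harm as benefit, or that its efficacy conclusion is inverted. The article does not support that. The hypothesis states the direction plainly, so the intended reading is recoverable. Efficacy rests on the time-by-group interaction, which this sentence does not touch. Nor does a positive coefficient mean that participants who became fitter became more suicidal. It is conditional on arm, and it would also arise if risk fell in everyone but fell less in those who gained most.

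**Conclusion.** The criterion and the outcome as described are inconsistent. On the ordinary reading, support for Hypothesis 1.2 needs a negative coefficient and the article asks for a positive one. The consequence is a complete reversal of how the result is read for one of four hypotheses, with no change in the size of the estimate, the two-sided p-value, the sample size or the primary efficacy analysis.

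The conclusion rests on two assumptions: that change from baseline means follow-up minus baseline for both variables, and that the suicide-risk score in the model runs higher-worse, as the article shows for ideation severity. If the authors intended a reduction score, the defect is an unstated outcome coding and the word *positive* is right.

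**What to change.** Make one of two changes in the paragraph of Data analyses that gives this model:

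1. State that change is follow-up minus baseline for both suicide risk and VO2max, that a higher suicide-risk score means higher risk, and replace *positive* with *negative*; or
2. Define the outcome as reduction in suicide risk, baseline minus follow-up, keep VO2max change as follow-up minus baseline, and keep *positive*.

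Either is sufficient. The cost is one clause, to be recorded before the outcome data are analysed. Data collection, sample size, the covariates and the contemporaneous timing of the two changes can stay as they are.
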